### Participants

Participants must fulfil the following inclusion criteria: a) diagnosis of possible or probable DLB or MCI-DLB according to the established McKeith criteria from 2017 and 2020, respectively (McKeith et al., 2017; IG et al., 2020), b) are in age range between 50 and 85 years, c) have MMSE score > 15 at screening, d) are on stable doses of antiparkinsonian or dementia or psychiatric medications at least 1 month prior to the study initiation, e) participant or participant’s caregiver are able to give informed consent to actual and further assessments and procedures and f) have a responsible caregiver >18 years old who has contact with the participant at least three times a week.

The main exclusion criteria are a) any clinically significant or unstable psychiatric, medical or surgical condition, b) major cardiovascular or cerebral event that occurred within 6 months prior to the first visit, c) advanced malign disease or other terminal illness, d) relevant medication, alcohol or drug abuse, e) known sensibility to or contraindication for ABX, f) female participants who are pregnant or currently breastfeeding, and g) not able to proceed with the study regime (i.e., like traveling to study site or dysphagia, or unable to perform supplementary examination because of contraindications, claustrophobia, etc.). For other detailed inclusion and exclusion, criteria see Table 2.

**Table 2 tab2:** Inclusion and exclusion criteria in the ANeED study.

Inclusion criteria	1. Age ≥ 50 and ≤ 85 years of age, both gender
	2. Confirmed diagnosis of DLB including mild cognitive impairment in DLB (DLB-MCI).
	3. MMSE score >=15 at screening
	4. Able and willing to provide informed consent prior to any study related assessments and procedures
	5. Capable of complying with all study procedures
	6. Willing to provide blood samples for genetic analyses of APOE and GBA
	7. Willing and able to self-administer or administer by a caregiver oral ambroxol medication, from day 1 to study end (at 60 mg TID (day 1-7), 120 mg TID (day 8- 14), 315 mg BID (day 15-21), 315 mg TID (day 22-28) and 420 mg TID (day 29-550)).
	8. Contact with caregiver at least 3 times a week, to ensure sufficient information from the caregiver regarding participant’s status and possible change in condition
	9. Able to travel to the participating study site
	10. A female participant is eligible to participate if she is of non-childbearing potential or if women is of childbearing potential must use accepted contraceptive methods
	11. Caregiver needs to be ≥ 18 years when signing the informed consent form
Exclusion criteria	1. Current treatment with anticoagulants (e.g. warfarin, argatroban, dabigatraneteksilat, rivaroksaban, apiksaban, edoksaban)
	2. Current use of IMP or participation in another interventional clinical trial
	3. Exposure to more than three IMP within 12 months prior to the first dose in the current study
	4. Confirmed dysphagia that would preclude self-administration of ambroxol up to six tablets/d for the duration of this study
	5. Known sensitivity to the study medication, ambroxol or its excipients (lactose monohydrate, granulated microcrystalline cellulose, silicon dioxide, magnesium stearate and denatonium benzoate)
	6. History of known rare hereditary disorders of galactose intolerance: lactase deficiency or glucose-galactose malabsorption
	7. History of severe substance abuse (drug abuse or alcohol)
	8. Donation of blood (1 unit or 350 ml) within three months prior to receiving the first dose of the study drug
	9. Pregnant or breastfeeding
	10. Any clinically significant or unstable medical or surgical condition that may put the participant at risk when participating or may influence the results of the study or affect the participant’s ability to take part in the study. Such conditions may include:
	a) impaired renal function defined by eGFR<=30
	b) moderate/severe hepatic impairment defined by Child-Pugh score >1
	c) a major cardiovascular event (e.g. myocardial infarction, acute coronary syndrome, decompensated congestive heart failure, pulmonary embolism, coronary revascularisation that occurred within 6 months prior to the screening visit)
	d) Major stroke
	e) Major depression defined clinically or by GDS-15 >=11 points or delirium or psychotic disorder unrelated to DLB.
	f) Cancer, history of metastatic cancer, terminal illness or clinically significant disease within ≤5 years, except for adequately treated basal cell skin cancer.
	11. Planned major surgical treatment during the study period

APOE, apolipoprotein epsilon; BID, twice a day; DLB, dementia with Lewy bodies; DLB-MCI, mild cognitive impairment in DLB; eGFR, estimated glomerular filtration rate; GDS, the Geriatric Depression Scale; IMP – investigational medicinal product, PD, Parkinson’s disease, PDD, dementia in PD; MMSE, Mini Mental State Examination; TID, three times a day.

If the patient at a later time point is no longer eligible to participate in the study as a result of a change in health status that does not align with the inclusion or exclusion criteria, the principal investigator (PI) will decide if the deviation will result in exclusion from the scheduled follow-ups. Minor deviations, such as a recently developed depression or cognitive decline on the Mini Mental State Examination (MMSE) <15, provide no solid base for exclusion. Major deviations, such as a change in diagnosis DLB (e.g., to non-DLB) may result in exclusion from the study.

To assess informal caregivers’ stress, we wish to invite them to join the study. Informal caregivers to join the study as well. Informal caregivers are eligible to join if they are spending time with the patient at least three times a week.

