### Randomisation and blinding

We will perform randomisation using the electronic case report form (eCRF) system (Viedoc^1^). The participants will be randomly assigned into two arms: ABX 1260 mg/d (in three doses per day) and placebo – in an allocation ratio of 1:1. Before randomisation, the participants will be stratified due to risk factors (number of APOEε4 alleles (0, 1, 2) and beta-amyloid in CSF: normal and low). Therefore, we will use a restricted randomisation method with blocking and stratification. The number of strata is six. The block size is 4 (McKeith et al., 2017) with number and blocks 6 (Webb et al., 2003). The independent data manager will provide randomisation, and the drug manufacturer will get the list and deliver drug kits numbered based on the stratification.

The patients, patient’s caregivers, all study personnel, monitors and statisticians are blinded until the end of the study, with the exception of an emergency unblinding procedure. The ABX and placebo are produced in a tablet form and identical in appearance and taste to blinding purposes. Placebo tablets with microcrystalline cellulose as the main compound will include denatonium benzoate as a residual amount of bitter substance as ABX tablets have. Each participant will get the investigation medical product (IMP) in sequentially numbered identical containers according to the randomisation schedule. The responsible pharmaceutical company, Kragerø Tablettproduksjon AS, will send IMP shipments directly to each participating centre for dispensing and storage for the study.

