### Primary outcome

The primary outcome is the mean score on the MMSE-N3 at 18 months in the intervention group compared to the control group. Secondary outcomes are as follows:

1. To establish safety and tolerability of the ABX in high doses. The endpoints are the number of participants withdrawing the study medication in ABX and placebo groups, the number of participants requiring reduction of dosage due to possible AE in ABX and placebo groups and the number and characterisations of AEs in both study arms.2. To establish the effect of ABX in subgroups of participants diagnosed with DLB measured by MMSE-NR3 in ABX and placebo groups dependent on stratified risk for concomitant beta-amyloid pathology defined by *APOE* status and beta-amyloid (Aβ_1-42_) levels in CSF.3. To assess the effect of ABX on the results of neuropsychological tests (change from baseline to 18 months in mean scores for the clock drawing test, COWAT immediate and delayed recall, TMT A and B, VOSP silhouettes and FAS test).4. To study the effect of ABX on the global functional decline measured by changes in CDR-SB at the baseline and after 18 months.5. To investigate the effect of the ABX on neuropsychiatric symptoms and depression measured by the mean change in the total NPI score and GDS, respectively, from baseline to the study end at month 18.6. To examine the effect of ABX on sleep disturbances, especially REM sleep behaviour disorders (RBD), frequency of falls, cognitive and awareness fluctuations, parkinsonism and autonomic functions. Endpoints are change in the number of participants with RBD defined from the MSQ, the frequency of falls at the baseline and study end, the change in the MFS and the mean change in the UPDRS motor part score at the baseline to month 18 in ABX and placebo arms.

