### Statistical methods

Full details of all planned statistical analyses will be included in a written statistical analysis plan (SAP), which will be completed before the final study database is locked for analysis. The SAP will specify those endpoints and will employ conventional frequentist methods (i.e., statistical significance tests). All final reports and publications will clearly identify and differentiate between pre-planned and post-hoc tests of statistical significance. When appropriate, value of p thresholds will be adjusted to compensate for increases in family-wise error rates associated with multiple testing. We will apply an ANCOVA, a linear model for MMSE at 18 months, depending on treatment adjusted for MMSE at baseline with a random intercept for randomisation stratification and block.

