## Discussion

Here, we present here our protocol for the ANeED study testing ABX in prodromal and mild DLB. Prodromal stages of DLB are now defined for research purposes and these individuals, including those with mild dementia and those who need to be offered inclusion in clinical trials to establish treatment options with disease modifying drugs in DLB.

The rationale for the use of ABX in DLB is firmly established and is based on both preclinical and clinical data. Because GCase activity is associated with aS metabolism, enhancing CMA may potentially reduce pathological aS depositions. Preclinical trials of ABX in models of synucleinopathies are promising and showing the effects of reducing the concentration of toxic aS species. ABX penetrate into CSF (Mullin et al., 2020) and first trials have shown an enhancing effect of ABX on GCase activity in human cells.

Our study is the largest ongoing clinical trial with ABX and the first in patients with prodromal and mild DLB. To date, we have included 47 patients in the study and 30 who started medication in the first 12 months; we observed good tolerability with only a few side effects. There are also seven candidates waiting for a screening visit.

One previous study on ABX in PD was carried out in only 17 participants, and it was not randomised or placebo controlled (Mullin et al., 2020); another is now completed with 50 patients with PDD (Silveira et al., 2019). The goal in our study is to recruit 180 participants, a number sufficient to find a difference between the active treatment group and the placebo group at 18 months based on the MMSE. However, 180 participants might not be enough to apply for a marketing authorisation if the study turns out to show the effect of ABX on DLB.

Based on our previous research, we know that the combined significant AD pathology in DLB will worsen prognosis; therefore, we decided to stratify the participants in our study based on APOEε4 genotypes and CSF Aβ_1-42_ to secure equal groups for placebo and ABX. We will also extend the study duration to 18 months and thereafter to 12 months of open extension to maximise the chances of showing treatment effects.

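### The investigator may end scheduled follow-up after a later change in health status or diagnosis, which can cause informative loss of the 18-month MMSE; outcome collection should be kept separate from that decision

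*Protocol article*

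**What the plan says.** The rule stands below Table 2 in the Participants section of the protocol article. Its trigger is a later change in health that takes the participant outside the eligibility criteria. In that case "the principal investigator (PI) will decide if the deviation will result in exclusion from the scheduled follow-ups".

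Two grades of deviation follow. Newly developed depression, or a fall in MMSE below 15, is called minor and is said to "provide no solid base for exclusion". The other grade reads: "Major deviations, such as a change in diagnosis DLB (e.g., to non-DLB) may result in exclusion from the study".

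Three other places bear on the point:

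- **Primary outcome:** "The primary outcome is the mean score on the MMSE-N3 at 18 months in the intervention group compared to the control group".
- **Statistical methods:** "We will apply an ANCOVA, a linear model for MMSE at 18 months, depending on treatment adjusted for MMSE at baseline".
- **Randomisation and blinding:** "all study personnel, monitors and statisticians are blinded until the end of the study", apart from emergency unblinding.

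Stopping study medication because of adverse events is handled separately, under Safety monitoring. Nowhere does the article say that a participant excluded under the Participants rule is still assessed at 18 months.

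**The concern.** The rule acts on events after randomisation and takes away visits, not only study drug. The events it covers can relate to treatment, to disease course, or to both. Table 2 includes renal and hepatic impairment, major cardiovascular events, stroke, delirium, dysphagia and ability to travel to the site. Revision of the diagnosis is also foreseeable. The trial admits possible DLB and MCI-DLB, and the Background says that symptoms are less specific in the prodromal stage.

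If participants who leave in this way have a different MMSE course from those who stay, and leave at different rates in the two arms, the completers are no longer comparable as randomised. The primary analysis uses one value per person, the MMSE at 18 months. If the visit is not held, earlier visits could support only imputation under assumptions that cannot be tested. This is why the point cannot wait for the analysis plan: that plan can choose a method, but it cannot supply the data.

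Safety is the first objective listed at the end of the Background. Ending visits after an organ-function or cardiovascular event could also cut the adverse event record short.

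**Working it through.** The plan gives no exclusion rate, so there is no figure of its own to reproduce on this point. Everything below that rests on a rate is an assumed illustration.

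**Inputs from the Sample size section:** target difference 3 MMSE points, SD 5.7, 25% drop-out, 180 randomised. Two-sided alpha of 0.05 is assumed, since none is stated. With these inputs the usual formula gives 2 × 5.7² × (1.960 + 0.842)² / 3² = 56.7, so 57 per arm, 114 in total, and 114 / 0.75 = 152 after drop-out. That is not 180. The mismatch is a separate matter, and 180 serves here only as the number randomised.

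**1. Shift from unequal exclusion.** If a fraction e of an arm is excluded and its mean lies D points from the mean of the whole arm, the mean of those left shifts by e × D / (1 − e). With D = 5 (assumed):

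| Excluded | Shift in arm mean |
|---|---|
| 2% | 0.02 × 5 / 0.98 = 0.102 |
| 6% | 0.06 × 5 / 0.94 = 0.319 |
| 8% | 0.08 × 5 / 0.92 = 0.435 |

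- 2% against 6%: 0.319 − 0.102 = 0.217 points, and 0.217 / 3 = 7% of the target.
- 2% against 8%: 0.435 − 0.102 = 0.333 points, and 0.333 / 3 = 11% of the target.

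**2. Range.** If g is instead the gap between retained and excluded participants, the shift is (difference in exclusion share) × g.

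- 10% against 5%: 0.05 × 3 = 0.15 to 0.05 × 5.7 = 0.29 points.
- 15% against 5%: 0.10 × 3 = 0.30 to 0.10 × 5.7 = 0.57 points.
- Equal shares and equal gaps: zero.

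**3. Scale against sampling error.** Completers: 180 × 0.75 = 135, or 67.5 per arm. The unadjusted standard error of the difference is 5.7 × √(2 / 67.5) = 0.98. A shift of 0.22 to 0.33 points is therefore about a fifth to a third of one standard error.

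**4. Simulation** (2,000 replicates, 180 randomised, ANCOVA). Baseline mean was 23, mean decline 3 and residual SD 5.7. The baseline SD of 3.5 is assumed. Exclusion depends on decline: 30% of the worst-declining quartile and 2% of the others leave. In the unequal case the placebo rate in the worst quartile is 5%.

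| Exclusion | Estimate, true effect 0 | Type I error | Estimate, true effect 3 |
|---|---|---|---|
| None | −0.03 | 5.0% | 2.99 |
| Same rule in both arms | −0.01 | 6.1% | 2.80 |
| Unequal between arms | +0.50 | 8.9% | 3.39 |

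Under no effect, the same rule in both arms leaves the estimate about unbiased. Under a true effect of 3, the same rule gives 2.80, because fewer treated participants then fall in the worst quartile and the arms lose different numbers.

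**5. Power.** With 135 completers, power for 3 points is 86.4%. If such exclusions came on top of the 25%, power would be 81.2% with 10% extra loss (117 completers) and 78.1% with 15% extra (108 completers).

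**The case against.** The strongest case on the other side has five parts.

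- **The rule is discretionary.** The investigator decides, and a major deviation only may lead to exclusion. A reader might infer that outcomes will be deleted and the randomised comparison broken. The text does not support that: it permits the loss without requiring it. This part stands.
- **The plan has safeguards.** Study personnel are blinded, which prevents knowing selection by arm. The statement on depression and MMSE below 15 largely closes the most direct outcome-driven route. Both stand, but neither covers a change of diagnosis or the remaining criteria, and blinding does not stop event rates from differing between arms.
- **The direction is not fixed.** A reader might infer from the Discussion, where "we know that the combined significant AD pathology in DLB will worsen prognosis", that participants relabelled as non-DLB would be the fast decliners. That sentence concerns AD pathology within DLB and explains the stratification. It says nothing about relabelled participants. The Background also says that DLB declines faster than AD, so a participant relabelled as AD could be a slower decliner. This part stands.
- **The size is small and assumed.** No rate, gap or imbalance is given, and the larger simulated bias needed a sixfold difference between arms (30% against 5%). A reader might also add these exclusions to the 25% drop-out, but the Sample size section does not say that they are left out of it. This stands, so the power figures above are conditional.
- **The article condenses a longer protocol.** Procedures after exclusion may be described there. But the article states a rule about follow-up, which is more than silence. If the full protocol keeps collecting outcomes, the two texts need to be aligned.

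**Conclusion.** The point holds as a risk that the rule creates. The investigator may end scheduled follow-up, or participation, after changes that arise once treatment has begun. The primary ANCOVA needs an 18-month MMSE, and the article does not keep collecting it in these participants. Neither the occurrence nor the direction of bias can be established from the documents.

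Under the assumed rates (2% against 6% to 8%, with a 5-point gap) the shift is 0.22 to 0.33 points, or 7% to 11% of the target difference. With equal exclusion and no treatment effect it is about zero. The illustration shows a modest effect that could be larger if exclusion were very unequal.

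This should be fixed, because the remedy is cheap and the loss cannot be repaired afterwards. The documents do not support calling it a demonstrated bias or a defect that invalidates the trial.

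**What to change.** Amend the rule in the Participants section as follows:

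- A later change in eligibility or diagnosis does not by itself end outcome collection.
- Any decision on study drug remains clinical and is separate from follow-up.
- At least the 18-month MMSE, and safety follow-up where feasible, is sought from every randomised participant who has not withdrawn consent. The full visit schedule need not be compulsory, since some changes, such as terminal illness or inability to travel, may make it impracticable.
- These participants are included in the primary comparison as randomised. Those whose diagnosis was revised may be left out in a sensitivity analysis only, which still answers the question about a diagnostically purer sample.

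The cost is a short amendment, an instruction to the seven sites, and a few extra visits. The Discussion reports 47 participants included at the time of writing, out of a planned 180, so at that point most follow-up still lay ahead.

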### Recruitment

We plan to recruit participants primarily through specialists or delegated trained clinicians working in the study’s sites: memory outpatient’s clinics, geriatrics clinics, and old age psychiatry clinics or during routine standard of care outpatient appointments at participating sites. The PI or delegated clinician in each of the participating centres will clinically evaluate whether participants fulfil all inclusion criteria without any counterindications. Haugesund Hospital is the appointed participant identification centre (PIC) and refers all potential participants to their local site after national patient and public involvement (PPI) initiatives. Additionally, all sites will identify their own local participants.

As an additional recruitment alternative, we will apply for ethical approval to search medical records for patients attending our sites during the last 12 months to be contacted for screening. If the projected study sample size turns out to be low, we will also engage the PPI program, which will focus on patient recruitment through various media channels (paper, TV and other advertisements).

### Randomisation and blinding

We will perform randomisation using the electronic case report form (eCRF) system (Viedoc^1^). The participants will be randomly assigned into two arms: ABX 1260 mg/d (in three doses per day) and placebo – in an allocation ratio of 1:1. Before randomisation, the participants will be stratified due to risk factors (number of APOEε4 alleles (0, 1, 2) and beta-amyloid in CSF: normal and low). Therefore, we will use a restricted randomisation method with blocking and stratification. The number of strata is six. The block size is 4 (McKeith et al., 2017) with number and blocks 6 (Webb et al., 2003). The independent data manager will provide randomisation, and the drug manufacturer will get the list and deliver drug kits numbered based on the stratification.

The patients, patient’s caregivers, all study personnel, monitors and statisticians are blinded until the end of the study, with the exception of an emergency unblinding procedure. The ABX and placebo are produced in a tablet form and identical in appearance and taste to blinding purposes. Placebo tablets with microcrystalline cellulose as the main compound will include denatonium benzoate as a residual amount of bitter substance as ABX tablets have. Each participant will get the investigation medical product (IMP) in sequentially numbered identical containers according to the randomisation schedule. The responsible pharmaceutical company, Kragerø Tablettproduksjon AS, will send IMP shipments directly to each participating centre for dispensing and storage for the study.

